# Steroid treatment as anti-inflammatory and neuroprotective agent following out-of-hospital cardiac arrest: a randomized clinical trial

**DOI:** 10.1186/s13063-022-06838-0

**Published:** 2022-11-22

**Keywords:** Acute cardiac care, Out-of-hospital cardiac arrest, Pre-hospital intervention, Randomized controlled trial, Post cardiac arrest syndrome, Inflammation, Neuroprotection, Steroid, Hemodynamics

## Abstract

**Background:**

Patients resuscitated from out-of-hospital cardiac arrest (OHCA) have a high morbidity and mortality risk and often develop post-cardiac arrest syndrome (PCAS) involving systemic inflammation. The severity of the inflammatory response is associated with adverse outcome, with anoxic irreversible brain injury as the leading cause of death following resuscitated OHCA. The study aimed to investigate the anti-inflammatory and neuroprotective effect of pre-hospital administration of a high-dose glucocorticoid following OHCA.

**Methods:**

The study is an investigator-initiated, randomized, multicenter, single-blinded, placebo-controlled, clinical trial. Inclusion will continue until one hundred twenty unconscious OHCA patients surviving a minimum of 72 h are randomized. Intervention is a 1:1 randomization to an infusion of methylprednisolone 250 mg following a minimum of 5 min of sustained return of spontaneous circulation in the pre-hospital setting. Methylprednisolone will be given as a bolus infusion of 1 × 250 mg (1 × 4 mL) over a period of 5 min. Patients allocated to placebo will receive 4 mL of isotonic saline (NaCl 0.9%). Main eligibility criteria are OHCA of presumed cardiac cause, age ≥ 18 years, Glasgow Coma Scale ≤ 8, and sustained ROSC for at least 5 min. Co-primary endpoint: Reduction of interleukin-6 and neuron-specific-enolase. Secondary endpoints: Markers of inflammation, brain, cardiac, kidney and liver damage, hemodynamic and hemostatic function, safety, neurological function at follow-up, and mortality. A research biobank is set up with blood samples taken daily during the first 72 h from hospitalization to evaluate primary and secondary endpoints.

**Discussion:**

We hypothesize that early anti-inflammatory steroid treatment in the pre-hospital setting can mitigate the progression of PCAS following resuscitated OHCA. Primary endpoints will be assessed through analyses of biomarkers for inflammation and neurological damage taken during the first 72 h of admission.

**Trial registration:**

EudraCT number: 2020-000855-11; submitted March 30, 2020

ClinicalTrials.gov Identifier: NCT04624776; submitted October 12, 2020, first posted November 10, 2020

## Administrative information

Note: this protocol’s numbers in curly brackets refer to SPIRIT checklist item numbers. The order of the items has been modified to group similar items (see http://www.equator-network.org/reporting-guidelines/spirit-2013-statement-defining-standard-protocol-items-for-clinical-trials/).

## Introduction

### Background and rationale {6a}

Each year, approximately 5000 individuals suffer from out-of-hospital cardiac arrest (OHCA) in Denmark, and despite an improved prognosis, 30-day mortality is approximately 85% [1]. For unconscious OHCA patients admitted to an intensive care unit (ICU) after successful resuscitation, the 30-day mortality remains higher than 50% [2, 3].

Unconscious patients resuscitated from OHCA often develop a complicated systemic response, called post-cardiac arrest syndrome (PCAS) [4, 5]. PCAS consists of four interacting components: (1) ischemic/reperfusion brain injury with possible development of brain edema, (2) myocardial dysfunction, (3) a systemic inflammatory response, and (4) persistent stress from the triggering cause of the cardiac arrest, e.g., acute myocardial infarction (AMI) [4]. PCAS progresses during the first days in unconscious patients following resuscitated cardiac arrest, and the treatment aims to reduce neurologic injury by targeted temperature management, circulatory support with vasopressors, and inotropics or mechanical devices as well as identification and treatment of reversible causes to the cardiac arrest, e.g., acute revascularization of an AMI [5, 6].

Several studies have shown that the systemic inflammatory response is associated with a high risk of poor outcome following OHCA in unconscious patients [7–9]. Despite this, no specific treatment targets this complicated and life-threatening inflammatory response, and guidelines remain inconclusive in this field.

Anoxic irreversible brain injury remains the leading cause of death in unconscious patients following resuscitated OHCA [10, 11], and it is thought to develop due to neuron apoptosis and reperfusion/ischemic injury [4, 12]. Inhibiting the causes of the anoxic brain injury in the early stages following resuscitation from OHCA may therefore be key to optimizing post-cardiac arrest care.

Inflammatory markers associated with poor outcome include interleukin (IL) 6, high-sensitivity C-reactive protein (hsCRP), leucocytes, IL-1b, IL-10, IL-13, tumor-necrosis factor (TNF) α, and procalcitonin [7, 13, 14].

The biomarker neuron-specific enolase (NSE) correlates to neuron damage in the blood stream and has a strong predictive value for poor outcome following OHCA [15, 16].

Following resuscitated OHCA, the function of the adrenal gland is compromised due to global ischemia, and accordingly, reduced levels of the steroid glucocorticoid are produced [17, 18]. Glucocorticoid has an important role in several physiologic processes including a systemic anti-inflammatory response [19, 20]. As a result, resuscitated cardiac arrest patients are affected by a severe inflammatory response, while the body’s natural defense mechanism to modulate inflammation is suppressed.

Systemic treatment with glucocorticoids serves as an anti-inflammatory mediator. It counteracts acute microcirculation injury and free radical formation, resulting in diminished vasodilation and reduction of edema, e.g., brain edema [20–22]. These anti-inflammatory effects are mediated through a slow genomic response (hours) and a rapid non-genomic response (seconds/minutes) [23]. Two former small studies have shown signs of improved survival and neurologic outcome among patients who were given injections with glucocorticoids after in-hospital cardiac arrest (IHCA) [24, 25] and a similar contemporary study found an association between glucocorticoids and higher rates of return of spontaneous circulation (ROSC) but with no impact on survival [26]. The incidence of adverse events was not higher in patients receiving glucocorticoids in the three studies. Long-term treatment with glucocorticoids is associated with a series of side effects, whereas short-term treatment only has limited side effects [27]. Short-term systemic treatment with glucocorticoids could therefore be an essential and safe factor in the acute treatment of resuscitated cardiac arrest patients that could potentially improve survival and neurological outcome [22].

In summary, PCAS is a life-threatening condition following resuscitated OHCA that involves a systemic inflammatory component. PCAS and the level of inflammation are associated with increased mortality and poor neurological outcome. Inhibition of this inflammatory response may have an important, yet relatively unknown, role in post-cardiac arrest care. Early treatment following resuscitation with the anti-inflammatory glucocorticoid methylprednisolone in the pre-hospital setting could mitigate inflammation through non-genomic pathways and thereby prevent further development of PCAS, leading to improved outcome.

### Objectives {7}

#### Primary objective

The primary objective is to determine the efficacy of methylprednisolone compared with placebo administered after ROSC on outcome parameters: daily IL-6 and NSE levels from admission to 72 h later, in comatose, resuscitated OHCA patients.

#### Secondary objectives

The secondary objectives are to determine the effects of methylprednisolone on markers of inflammation, cardiac protection, neuroprotection, renal protection and endothelial protection, clinical endpoints including survival and neurological outcome, and safety. Quantification of secondary objects is specified in the “Outcomes {12}” section.

#### Hypothesis

Bolus infusion of 250 mg methylprednisolone in the pre-hospital setting will inhibit the systemic inflammatory response and reduce biomarkers of the degree of cerebral injury in comatose, resuscitated OHCA patients.

### Trial design {8}

The study was designed as an investigator-initiated, 1:1 randomized, multicenter, blinded, placebo-controlled phase II clinical superiority trial.

## Methods: participants, interventions, and outcomes

### Study setting {9}

Multicenter study carried out at the following sites:The Cardiac ICU at the Department of Cardiology, The Heart Centre, Copenhagen University Hospital—Rigshospitalet, CopenhagenThe ICU, Copenhagen University Hospital—Gentofte Hospital, CopenhagenThe Emergency Medical Services of the Capital Region of Denmark—Copenhagen

### Eligibility criteria {10}

All resuscitated OHCA patients in the Capital Region of Denmark are screened for eligibility. The screening is performed by the on-duty physician manning the mobile critical care unit (CCU). The Danish Cardiac Arrest Registry will be used as a screening log during the trial. Following successful screening, the patient will be included, and study drug will be given. Inclusion in the STEROHCA trial does not prohibit participation in other trials.

#### Inclusion criteria

Age ≥ 18 yearsOHCA of presumed cardiac causeUnconsciousness (GCS ≤ 8) upon pre-hospital randomizationSustained ROSC for at least 5 minRandomization and start of study medicine infusion within 30 min of sustained ROSC

#### Exclusion criteria

Advanced life support termination-of-resuscitation (TOR) exclusion criteria [28, 29].Asystole as primary electrocardiogram (ECG) rhythmWomen of childbearing potentialKnown therapy limitation (known decision made of no resuscitation or intensive therapy)Known allergy to methylprednisoloneKnown pre-arrest modified Rankin Scale (mRS) score of 4–5Temperature upon randomization < 30° C > 30 min to sustained ROSC

### Who will take informed consent? {26a}

The trial will be conducted in accordance with the Declaration of Helsinki and follow European and national legislation on medical research in emergency situations with subjects temporarily incapacitated. Since subjects are incapacitated, they will not be able to provide informed consent prior to enrollment. According to Danish legislation, a proxy consent from a legal surrogate (trial guardian) is required on behalf of the patient prior to inclusion. The trial guardian providing informed consent will be a medical doctor with no involvement in the patient treatment in this trial. The consent will be filled out through the encrypted database program REDCap. Further, informed consent from the next of kin will be obtained at the earliest time possible. The latter consent will be obtained by the physician on call or a dedicated team of research personnel, all medical doctors. A consent from a secondary trial guardian will be obtained following admission of the patient in REDCap. Approvals from the relevant authorities can be seen in section {24}.

### Additional consent provisions for collection and use of participant data and biological specimens {26b}

Approval from the local ethical committee will be needed for ancillary studies of patient data or biological specimens unless this is waived based on prior approvals or the design of the studies.

### Interventions {11}

#### Explanation for the choice of comparators {6b}

We have chosen a single bolus infusion of 250 mg methylprednisolone (Solumedrol) for attenuation of the inflammatory response seen following OHCA. Pulse doses of methylprednisolone (≥ 250 mg) are widely used in the treatment of conditions such as prevention of organ rejection after transplantation, rheumatic diseases with acute deterioration, multiple sclerosis, and acute injury of the bone marrow [30]. At methylprednisolone doses above 250 mg, infusion time should be above 30 min, whereas doses below 250 mg can be completed within 5 min, according to the Danish summary of product characteristics. Placebo is chosen as comparator since there is no known effective treatment targeting inflammation and neuroprotection in resuscitated OHCA patients.

#### Intervention description {11a}

Patients allocated to methylprednisolone will receive a bolus infusion of 250 mg over 5 min. The study drug is prepared by a simple shaking-mechanism where 2 × 125 mg/2 mL of methylprednisolone powder is mixed preservative-free to a total volume of 4 mL. Patients allocated to placebo will receive a 4 mL infusion of isotonic saline. Infusion of study drug or placebo will be made as soon as possible following 5 min of stable ROSC in the pre-hospital setting.

#### Criteria for discontinuing or modifying allocated interventions {11b}

If the next of kin or the trial guardian of a patient refuses or withdraws consent to participate in the study, the patient will be withdrawn from the trial without prejudice to future medical care. Further, if the patient refuses or withdraws consent, when able to, no study observations will be made from the date of request and the patient will be removed from the study.

A patient can be withdrawn from the study by the sponsor-investigator if any of the following occurs: (1) significant intercurrent illness, (2) patient refusal to continue observations, and (3) investigator decides that termination is in the best medical interest of the patient.

If withdrawal of consent occurs, observations will be completed to the date of withdrawal and a final evaluation of the patient’s withdrawal will be made at this point with an explanation for the withdrawal. If withdrawal is due to an adverse event, the patient will be followed until the adverse event is stabilized or resolved.

#### Strategies to improve adherence to interventions {11c}

All trial guardians and physicians including patients have relevant knowledge of the cardiological specialty and knowledge of the study from an obligatory instruction video and the handing out of the study protocol, protocol summaries, and pocket cards. None of these physicians are involved with the primary care of the patient following admission. The study medicine is a single bolus infusion administered over 5 min, and there is a low risk of missing or delaying the intervention following screening of the patient.

In-hospital personnel involved in the primary care of the patient, i.e., doctors and nurses, have relevant knowledge of the study through the instruction video and written instructions and have been trained in data collection study specific procedures.

#### Relevant concomitant care permitted or prohibited during the trial {11d}

According to temporary guidelines, all patients included in the study will be treated with standard therapies for OHCA, including targeted temperature management at 36 degrees, vasopressors and/or inotropes if needed and prophylactic antibiotics. Necessary cardiac interventions will not be delayed by the trial intervention. The specific care of all patients is left to the discretion of the treating physician.

#### Provisions for post-trial care {30}

Included patients will be insured by the Patient Compensation Association (the health system responsible for the trial sites, “Rigshospitalet” and “Gentofte Hospital”).

### Outcomes {12}

#### Primary outcome

The primary outcome is the repeated daily measurements of IL-6 and NSE at admission and the following 24, 48, and 72 h after admission.

#### Secondary outcomes

Markers of inflammation: hsCRP, leucocyte- and differential count, plasma cytokine levels (IL1b, IL-2, IL-4, IL-5, IL-7, IL-8, IL-10, IL-12, IL-13, IL-17A, GM-CSF, G-CSF, MCP-1, MIP-1beta, IFN-g and TNF-α), and procalcitonin measured daily the first 3 days from admission.

Markers of kidney and hepatic injury: Daily creatinine levels the first 3 days from admission. Daily measurements of ALAT, ASAT, ALP, bilirubin, and INR the first 3 days from admission.

Markers of the coagulation system (only at the site “Rigshospitalet”): Plasma fibrinogen the first three days from admission, and thromboelastography (TEG) at admission and at 48 h.

Protein and enzymatic protection: Daily proteomics and metabolomics samples the first 3 days from admission.

Hemodynamics: Daily evaluation by Swan-Ganz catheter (only at “Rigshospitalet”), bihourly analyses of arterial blood gasses the first 36 h and transthoracic echocardiogram (TTE) measured at time of admission and before hospital discharge.

Neuroprotection: Daily measurements of Tau and NfL levels the first 3 days from admission.

Cardiac protection: Measurements of TnT (at “Rigshospitalet”), TnI (at “Gentofte Hospital”), and CKMB levels at admission and the following 6, 12, 24, 36, 48, and 72 h of admission.

Clinical endpoints: Daily Sequential Organ Failure Assessment (SOFA) scores the first 3 days from admission. Survival and neurological outcome, decided by CPC and mRS score after 5 days, at discharge from the intensive ward and the hospital and following a minimum of 180 days from discharge through telephone interview.

Follow-up at 90 days following discharge in an ambulatory setting: MoCA-score for assessment of cognitive function and patients will be screened for quality of life, anxiety, depression, and the return to daily living with their nearest relatives.

Safety: Cumulated daily incidence of any adverse event (AE) the first 7 days, including “severe adverse event” (SAE), and “adverse event with believed relation to the study medicine” (SUSAR).

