	**Trial period**							
	**Enrolment**	**Post-allocation**						**Follow-up**
**Timepoint**	*0 h*	*6 h*	*12 h*	*24 h*	*36 h*	*48 h*	*72 h*	*Days 90 and 180*

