**Assessments**								
**Biochemistry**^**a**^	x	x	x	x	x	x	x	
**Biobank samples**	x			x		x	x	
**ECG**	x	x	x	x	x	x	x	
**Swan-Ganz-based measurements**	x	x	x	x	x	x	x	
**Echocardiography**				Day 1				Before discharge
**ABG and VBG**^**b**^	x	x	x	x	x	x	x	
**SOFA score**				x		x	x	
**CPC and mRS score**								x
**MoCA score**								Only day 90

*ABG* Arterial blood gas, *CPC* Cerebral Performance Category, *ECG* Electrocardiogram, *mRS* Modified Rankin Score, *MoCA* Montreal Cognitive Assessment, *SOFA* Sequential Organ Failure Assessment, *VBG* Venous blood gas

^a^Details in outcomes section in the manuscript

^b^Additional blood gasses are taken bihourly until 12 h and at 18 h

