#### Participant retention and follow-up plan {18b}

Patients included are expected to remain in the ICUs the first three days of admission until the primary endpoints are collected. If a patient awakes and is transferred to the ward, blood sampling will be done here, including samples for the research biobank to analyze the primary endpoints. If a patient is transferred to a local hospital within three days of admission, samples for the biobank are not taken but standard biochemistry will be taken routinely and will be collected. At both sites, dedicated staff will be responsible for follow-up in the ambulatory setting at approximately 90 days following OHCA. The patient will be offered a visit at home if an ambulatory visit is not possible or not wanted by the patient. Patients who discontinue the study during follow-up will remain in the study database if an informed consent is obtained. After 180 days patients will be evaluated through a telephone interview.

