## Trial status

Protocol: v3.1 of September 23, 2021

Recruiting status: First patient included on October 2020. Estimated recruitment completed in July 2022 and completion of 180 day follow up in January 2023.

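### The time origin of the 90- and 180-day secondary assessments is inconsistent: hospital discharge in the outcome list, the arrest in the retention plan (90-day visit), and by implication enrolment in Table 1

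*Protocol article*

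**What the plan says.** All references are to the protocol article.

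- **Secondary outcomes, clinical endpoints.** The assessments are "Survival and neurological outcome, decided by CPC and mRS score after 5 days, at discharge from the intensive ward and the hospital", and then a last one "following a minimum of 180 days from discharge through telephone interview".
- **Secondary outcomes, ambulatory visit.** MoCA, quality of life, anxiety, depression and return to daily living are collected at "Follow-up at 90 days following discharge in an ambulatory setting".
- **Participant retention and follow-up plan {18b}.** Staff at both sites arrange "follow-up in the ambulatory setting at approximately 90 days following OHCA". For the later contact the section says only "After 180 days patients will be evaluated through a telephone interview", without saying from when.
- **Table 1.** The time axis begins at enrolment (0 h). Its follow-up column is headed "Days 90 and 180". The row "CPC and mRS score" is marked in that column, and MoCA is restricted to day 90.
- **Recruitment {15} and Trial status.** Enrolment is followed by six months of follow-up. The calendar reads "Estimated recruitment completed in July 2022 and completion of 180 day follow up in January 2023".

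**The concern.** One visit has two printed origins. Staff who follow the outcome list and staff who follow the retention plan would book the same patient on dates that differ by the whole hospital stay.

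Discharge is also a weak origin for a randomized comparison, for two reasons.

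1. It happens after randomization. If treatment changed length of stay, the arms would be assessed at different times since arrest. The protocol itself monitors length of stay at the interim safety look (Interim analyses {21b}).
2. A patient who dies in hospital has no discharge from which to count, so the last CPC/mRS assessment has no literal date for that patient.

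The Discussion says the results should inform whether a larger trial powered for survival and neurological outcome is needed. These secondary endpoints are what such a trial would draw on, so it should be clear when they were measured and in whom.

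**Working it through.** The plan gives no figure to reproduce here. The check sets the sections side by side and then does date arithmetic.

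**1. Origins compared**

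| Assessment | Outcome list | Retention plan {18b} | Table 1 |
|---|---|---|---|
| Ambulatory visit (MoCA, quality of life) | 90 days from discharge | about 90 days from arrest | day 90, axis from enrolment |
| Last survival/CPC/mRS contact | at least 180 days from discharge | 180 days, no origin given | day 180, axis from enrolment |

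The first row is an outright contradiction between two sections. In the second row no section states an arrest origin in words; the conflict arises only through the axis of Table 1.

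**2. Time since arrest under a discharge origin**

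Formula: days since arrest = hospital stay + 90 (visit), or at least hospital stay + 180 (interview). The documents do not give length of stay, so a range of 5 to 60 days is assumed.

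| Assumed stay (days) | 90-day visit | Interview, earliest |
|---|---|---|
| 5 | 5 + 90 = day 95 | 5 + 180 = day 185 |
| 30 | 30 + 90 = day 120 | 30 + 180 = day 210 |
| 60 | 60 + 90 = day 150 | 60 + 180 = day 240 |

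The spread is 150 − 95 = 55 days for the visit, and 240 − 185 = 55 days for the earliest interview date. With an arrest origin, patients are due at about days 90 and 180 whatever their stay.

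**3. Does the calendar settle the origin?**

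- Enrolled 31 July 2022: arrest + 180 days is 27 January 2023. Discharge + 180 days is 1 February 2023 after a 5-day stay and 26 February 2023 after a 30-day stay. This favours an enrolment origin.
- Enrolled 1 July 2022 with a 30-day stay: discharge + 180 days is 27 January 2023, which is still within the stated month.

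The planned dates are estimates in whole months, so they support an enrolment origin only weakly.

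**4. Where in-hospital deaths are and are not covered**

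- Covered: the day-5 assessment, and the Kaplan–Meier, log-rank and Cox analyses in Statistical methods {20a}, where a death counts at its own time.
- Not covered by the literal wording: the assessment at least 180 days after discharge.
- The planning section expects about 20% of patients to die within 72 h (Sample size {14}), so patients without a discharge date will not be rare.

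**The case against.** The strongest reply is that this is one inconsistent phrase about secondary outcomes in a phase II trial, and that more can be read into it than the text bears. Four readings are tempting and are not supported.

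- **That the 180-day interview is explicitly timed from the arrest elsewhere.** It is not. The only stated arrest origin belongs to the 90-day ambulatory visit. Table 1 is described as schematic and only implies enrolment.
- **That in-hospital deaths are lost, or that the comparison shrinks to discharged patients.** Day 5 is defined for everyone and the time-to-event analyses count every death. Statistical methods {20a} assigns secondary outcomes to the intention-to-treat population, while section {20c} names the modified one. Neither restricts analysis to discharged patients.
- **That about half of the patients would have no origin.** The figure above 50% in Background and rationale is 30-day mortality among unconscious patients admitted to intensive care. This trial excludes asystole as primary rhythm and more than 30 min to sustained ROSC, and it expects some patients to wake and not need intensive care. The figure is not this trial's in-hospital mortality.
- **That the calendar proves an arrest origin.** The 1 July example shows otherwise.

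It is also fair to say that visit windows and the coding of deaths are details an article commonly leaves to the full protocol or analysis plan. The lack of an upper window is therefore not counted as a fault in itself.

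These replies limit the reach of the point. They do not remove the contradiction over the 90-day visit, and they do not make discharge a sound origin for comparing randomized arms.

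**Conclusion.** The point holds in this limited form. The origin is contradictory in words for the 90-day visit and by implication for the 180-day CPC/mRS contact. If the outcome list is followed, patients are assessed at unequal times since arrest: days 95 to 150 for the visit and days 185 to 240 at the earliest for the interview, on the assumption of stays from 5 to 60 days. Any difference in length of stay between the arms would carry over day for day into time since arrest. No such difference is shown, and none is claimed here. Patients who die in hospital never reach the discharge-based assessments, although the day-5 and time-to-event mortality results still include them.

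The co-primary IL-6 and NSE measurements, taken from admission to 72 h, are untouched. This is a correction the plan should make; it does not threaten the trial's main result.

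**What to change.** 1. Use one origin, the date of arrest (randomization), for the 90- and 180-day assessments. Word it the same way in Secondary outcomes, Table 1 and the retention plan {18b}.
2. State that the 180-day CPC/mRS comparison keeps all patients of the analysis population, with those dead by then counted in the worst category (CPC 5, mRS 6).
3. Where visits have already been made under a discharge origin, report actual days since arrest by arm.

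The cost is wording and scheduling. One drawback is that a few patients with long stays will be assessed while still in hospital or rehabilitation. Allocation is to be unblinded only after follow-up is complete and the database locked (Who will be blinded {17a}), so the analysis definition can be settled before then even if the visits themselves can no longer be moved.
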